## Abstract

**Background:**

Postoperative delirium may manifest in the immediate post-anaesthesia care period. Such episodes appear to be predictive of further episodes of inpatient delirium and associated adverse outcomes. Frontal electroencephalogram (EEG) findings of suppression patterns and low proprietary index values have been associated with postoperative delirium and poor outcomes. However, the efficacy of titrating anaesthesia to proprietary index targets for preventing delirium remains contentious. We aim to assess the efficacy of two strategies which we hypothesise could prevent post-anaesthesia care unit (PACU) delirium by maximising the alpha oscillation observed in frontal EEG channels during the maintenance and emergence phases of anaesthesia.

**Methods:**

This is a 2 × 2 factorial, double-blind, stratified, randomised control trial of 600 patients. Eligible patients are those aged 60 years or over who are undergoing non-cardiac, non-intracranial, volatile-based anaesthesia of expected duration of more than 2 h. Patients will be stratified by pre-operative cognitive status, surgery type and site. For the maintenance phase of anaesthesia, patients will be randomised (1:1) to an alpha power-maximisation anaesthesia titration strategy versus standard care avoiding suppression patterns in the EEG. For the emergence phase of anaesthesia, patients will be randomised (1:1) to early cessation of volatile anaesthesia and emergence from an intravenous infusion of propofol versus standard emergence from volatile anaesthesia only. The primary study outcomes are the power of the frontal alpha oscillation during the maintenance and emergence phases of anaesthesia. Our main clinical outcome of interest is PACU delirium.

**Discussion:**

This is a largely exploratory study; the extent to which EEG signatures can be modified by titration of pharmacological agents is not known. The underlying concept is maximisation of anaesthetic efficacy by individualised drug titration to a clearly defined EEG feature. The interventions are already clinically used strategies in anaesthetic practice, but have not been formally evaluated. The addition of propofol during the emergence phase of volatile-based general anaesthesia is known to reduce emergence delirium in children; however, the efficacy of this strategy in older patients is not known.

**Trial registration:**

Australian and New Zealand Clinical Trial Registry, ID: 12617001354370. Registered on 27/09/2017.

## Background and rationale

There is current interest in the use of electroencephalographic (EEG)-guided administration of anaesthesia to prevent postoperative delirium and neurocognitive decline, prompted by findings of the association between low intraoperative EEG index values or burst-suppression patterns and postoperative delirium [1–3]. The underlying rationale is that reducing total anaesthetic dose and avoiding EEG suppression might improve neurocognitive outcomes. Prospective randomised clinical trials (RCTs) comparing titration of anaesthesia to processed EEG index ranges versus clinical signs have demonstrated reductions in postoperative delirium [1, 4]. However, the merit of targeting particular EEG index values or patterns, compared to purely avoiding the suppression pattern, is not known.

In our previous observational work of EEG patterns during maintenance and emergence from general anaesthesia, we have observed a variety of patterns in the EEG prior to waking [5, 6]. Although there is not a consensus among anaesthesiologists of what it means to be awake, we have started to distinguish between emergence and recovery from general anaesthesia. When we use the term ‘emergence from anaesthesia’ we are referring to the transition from surgical anaesthesia to a state with outward signs of cortical function (typically coordinated motor responses). One example would be eye contact in response to verbal or light tactile stimulation. Anaesthesia recovery is the transition from the end of emergence to normal pre-operative neurocognitive function. Defining when the actual complete period of anaesthesia has ended, and the subject has returned to a pre-anaesthesia baseline is difficult because a patient may be safe to discharge from the recovery room before all of the sedating effects of anaesthesia have subsided. Therefore, the complete recovery trajectory may go undocumented.

We have previously found that delirium (or incomplete neurocognitive recovery) in the recovery room seems to occur less often when patients display stronger alpha (7–17 Hz) oscillations in the frontal EEG during the emergence phase of anaesthesia [5, 6]. However, frontal EEG alpha power during maintenance of anaesthesia is negatively correlated with pre-operative cognitive impairment [7] and with advancing age [8–10], and this could explain the propensity for postoperative delirium. Nevertheless, the extent to which the EEG alpha oscillation is subject to intraoperative pharmacological manipulation has, thus far, gone largely unexplored.

Previous EEG-based protective strategies have focussed on targeting proprietary dimensionless index values, the meaning of which are not well understood. However, the EEG alpha oscillation is a specific hallmark of gamma-amino-butyric-acid (GABA)-ergic anaesthesia [11]. Marked loss of frontal EEG alpha activity can occur in response to noxious stimulation [12, 13] and the frequency and power of alpha oscillations are sensitive to changes in effect-site concentrations of volatile agents and opioids [8, 14]. We hypothesise that a maximal EEG alpha oscillation during general anaesthesia may represent an ideal anaesthetic state of both adequate anti-nociception and appropriate anaesthetic depth, which would represent a novel, individualised, anaesthetic strategy.

We also plan to investigate the efficacy of an alternative strategy; transition to propofol during the emergence phase of anaesthesia on the EEG patterns observed during emergence from anaesthesia, with the aim of preventing abrupt transitions in brain state. This intervention has been shown to reduce the incidence of emergence delirium in young children [15, 16] but has not been investigated adequately in older populations. As well as looking at EEG features and trajectories, we will evaluate the effect of these interventions on relevant clinical outcomes, particularly the incidence of delirium in the post-anaesthesia care unit (PACU).

### Aims

To ascertain whether the EEG patterns observed in an elderly population are amenable to modulation by titration of commonly used anaesthetic agents during the maintenance and emergence phases of anaesthesia. We will assess the efficacy of (1) titration of anaesthesia to maximise the observed frontal EEG alpha oscillation and (2) the addition of propofol as the main hypnotic during emergence in preventing PACU delirium.

### Hypotheses

The frontal observed EEG alpha oscillation is amenable to modulation by active titration of desflurane and opioid intraoperativelyMaximisation of the EEG alpha oscillation during the maintenance phase of anaesthesia promotes more alpha activity during subsequent emergence from anaesthesiaSupplementation with intravenously administered propofol promotes alpha activity during the emergence phase of anaesthesiaAlpha-dominant EEG emergence trajectories are associated with a lower incidence and/or severity of PACU delirium and possibly later adverse clinical outcomes

### Secondary objectives

To confirm or refute previously observed associations between maintenance and emergence EEG features and PACU deliriumTo collect multichannel EEG recordings from a subset of patients to investigate associations between multichannel EEG markers and subsequent PACU deliriumTo collect additional detailed data for possible confounding factors, such as physiological insults (hypotension, blood loss, hypothermia, urinary catheterisation), as risk factors for PACU delirium, and create a statistical predictive modelTo investigate the prognostic utility of delirium scores and their subcomponents for subsequent adverse clinical outcomes and devise a specific PACU-delirium diagnostic toolTo detect abnormalities in speech-language function in PACU using an informal toolTo investigate whether the interventions have any effects on other early and late clinical outcomes such as early postoperative pain, recovery from surgery, serious adverse events and longer-term cognitive function

## Methods

### Sample selection and recruitment

Potential participants will be identified by screening of the operating theatre lists. In order to allow participants adequate time to decide if they wish to take part in the study we plan to approach patients in reasonable time before their surgery. This will be in person if they are admitted to the ward, or by a telephone call. The consent process will then be completed in person.

#### Inclusion criteria

Adults aged 60 years or over with capacity to provide informed consent who are undergoing elective non-cardiac surgery, which does not involve the head or neck, with planned volatile-based general anaesthesia of expected duration of at least 2 h

#### Exclusion criteria

Chronic pain with opioid requirement or concurrent use of enzyme inducers, e.g. carbamazepine, phenytoin, illicit substance use or excessive alcohol intake, refusal by patient or case anaesthetist responsible for patient’s care.

### Study design

This is a prospective RCT using a 2 × 2 factorial design stratified by pre-operative cognitive score and surgery type. The 2 × 2 design means that each patient has a 50% chance of being allocated to each intervention. This will result in four randomisation groups, each with equal numbers of participants, namely (A) maintenance *and* emergence interventions, (B) maintenance intervention only, (C) emergence intervention only and (D) neither intervention (Fig. 1). Figure 2 illustrates the planned data collection at each time point in the study.

**Fig. 1 Fig1:**
[figure not shown]
Study conduct flow sheet illustrating factorial design and data collection points

**Fig. 2 Fig2:**
[figure not shown]
SPIRIT diagram demonstrating planned data collection

### Randomisation and blinding

Assignment of study participants to intervention groups will be performed using block randomisation [17], stratified by cognitive status (determined by pre-operative Montreal Cognitive Assessment (MOCA) score), surgery type (vascular, orthopaedic and general/other) and site. Pre-operative cognitive impairment is widely recognised as a risk factor for postoperative delirium and we have previously found that delirium risk appears to be lower for non-spinal orthopaedic procedures [6]. The researcher collecting intraoperative EEG data will perform the randomisation, shortly prior to commencement of the anaesthesia episode. The case anaesthetists will not be blinded to the interventions. Participants will be blinded to their interventions. Members of the research team responsible for recruitment, baseline data collection and clinical outcome data observers for the PACU scores and follow-up data collection will be blinded to randomisation groups and intraoperative events. For final analysis of the primary EEG outcomes, the raw EEGs will be de-identified so that the researcher conducting the analysis cannot identify the individual participant or the group allocation. We do not anticipate unblinding will be necessary.

### First randomisation: maintenance phase of anaesthesia

Participants will be randomised to intraoperative oscillatory EEG alpha optimisation (Intervention 1) versus standard care (with burst suppression alert).

Intervention 1 involves real-time acquisition of oscillatory alpha power from the frontal EEG (recorded with the standard EEG electrode strip from the Entropy Module (GE Healthcare, Chicago, IL, USA) or the Bispectral Index (BIS) (Medtronic, Minneapolis, MN, USA) or other quantitative EEG monitor. An individual patient value for the maximal oscillatory alpha power ‘*Alpha Max*’ will be determined following induction of anaesthesia by variation of the end-tidal desflurane concentration prior to surgical incision. Effect-site concentrations of volatile and opioid will be estimated in real time to inform decisions around drug titration. During the intraoperative phase, we will aim to maximise oscillatory alpha EEG activity by individualised titration of desflurane and opioid. If alpha activity suddenly drops, the case anaesthetist will be advised to give a 0.5–1 mcg/kg bolus of fentanyl. Target end-tidal desflurane concentration will be adjusted according to real-time dose-response information. Typically, the concentration will be reduced in response to sustained loss of alpha activity; however, desflurane will not be reduced if quantitative EEG indices exceed a pre-defined threshold, to avoid awareness. For example, the State Entropy (SE) from the GE Entropy Module will be maintained below 60. The *Alpha Max* target will be adjusted intraoperatively if a new maximum is reached at any stage. The titrations will occur within prearranged limits agreed by the research team and the case anaesthetist and taking into account the clinical context, for example the degree of surgical stimulation.

For those patients randomised to standard care, anaesthesia will be conducted as per usual care by the anaesthetist, with quantitative processed EEG index values (e.g. State Entropy) and EEG waveforms visible as per the standardised protocol).

### Second randomisation: emergence phase of anaesthesia

Participants will be randomised to conversion to a propofol infusion for emergence from anaesthesia (Intervention 2) versus control (standard emergence from volatile anaesthesia).

This intervention will be achieved by infusion of propofol 400 mg/h and simultaneous reduction of inspired desflurane concentration during the final 10–20 min of surgery. Boluses of propofol may be given as required to keep acceptable quantitative EEG index values until surgery is complete. Total doses of propofol administered are likely to be in the range 1–3 mg/kg, which is comparable to the effective dose in children.

#### Primary outcomes

##### Intervention 1

Oscillatory EEG alpha power during the maintenance phase of anaesthesia

##### Intervention 2

Oscillatory EEG alpha power during the emergence phase of anaesthesia

Our primary trial outcomes are EEG outcomes (rather than clinical outcomes) because it is important firstly to determine whether the interventions, which are novel, do indeed have the anticipated effects on the intraoperative EEG parameters. Oscillatory alpha [12] is chosen as the outcome of neurophysiological interest because the total power in the frequency band is subject to general slowing of the EEG signal, and so the frequency of the alpha oscillation can drift outside the traditionally defined alpha frequency band.

#### Secondary outcomes

##### Intraoperative outcomes: EEG

Maintenance phase○ Proportion of time with EEG alpha power > 70% of *Alpha Max* (the maximal EEG alpha power)○ Burst suppression duration○ Quantitative EEG indicesEmergence phase○ EEG emergence trajectories○ Sequence and dynamics of slow wave (alpha and delta) activity and non-slow wave activity

We plan to evaluate the effectiveness of the intraoperative EEG alpha power-maximisation intervention by calculating the proportion of the maintenance phase during which the alpha oscillation is close to the maximum seen for that patient. This applies to the intervention group only since in the control group the maximal EEG alpha power will not be targeted. In addition to the primary outcome of oscillatory EEG alpha power, we will report on burst suppression and quantitative EEG indices. The EEG emergence trajectory patterns, in particular the presence or absence of abrupt state transitions, will also be categorised. A subset of patients will undergo multichannel EEG recording in addition to frontal EEG monitoring using locally available equipment, for later exploratory analyses.

##### Intraoperative outcomes: other

Total opioid and desflurane administered intraoperativelyTotal muscle relaxant doseHypotension (duration mean arterial pressure < 60 mmHg)

It is likely that the EEG alpha power-maximisation strategy will result in different patterns of administration of opioids and volatiles from the control group, which we will report. This could also result in differing muscle relaxant requirements and differences in intraoperative haemodynamic stability. In addition, we will collect feedback from the clinicians as to the acceptability of the protocol and the extent of any deviation from their usual care.

##### Immediate clinical outcomes: PACU

Interval from extubation to fit-for-discharge status (achievement of Post Anaesthesia Recovery Score (PARS) score of 10/12 or more) from PACUPACU delirium○ 3D-CAM (and 3D-CAM-Severity)○ 3D-CAM features○ Nursing Delirium Screening Scale (NuDESC)○ Richmond Agitation-Sedation Score (RASS)○ Confusion Assessment Method for the Intensive Care Unit (CAM-ICU)○ Speech-language screen○ Requirement for pharmacological and non-pharmacological management of deliriumPACU pain, nausea and vomiting○ Numerical rating score○ Opioid requirement○ Naloxone requirement

The ideal way to quantify neurocognitive recovery from anaesthesia is unclear so we intend to investigate a number of potential markers of both speed and quality of recovery. Extubation and fitness for discharge from PACU are easily recognised and readily recordable time points. A number of tools have been used to diagnose delirium in PACU, with variable performance [18, 19]. A *Diagnostic and Statistical Manual of Mental Disorders, fifth edition* (DSM-V) assessment by a trained physician or psychologist is usually considered the ‘gold standard’ for diagnosis of delirium; however, this is neither practical nor necessarily appropriate in the immediate post-surgical period; however, there is no single recommended PACU-delirium assessment tool [20]. The 3D-CAM [21] is a well-validated diagnostic instrument which we have found to be feasible in PACU in a small pilot study and this will be used as our main PACU-delirium outcome measure. In addition, we will perform the CAM-ICU, the NuDESC and a speech language screen to further cover the key neurocognitive domains. Our observations indicate that some patients experience language and/or cognitive communication deficits in PACU. Accordingly the inclusion of an informal speech-language screen may yield valuable information not typically obtained from delirium assessment tools. Tasks unique to this screen include category fluency, naming to definition and narrative production. Subsequent analysis of the later clinical outcomes will help to determine which features or scores are most important and of greatest prognostic value. Use of restraints or requirement of pharmacological treatment for PACU delirium will also be recorded. Since the EEG alpha power-maximisation strategy is hoped to maintain an optimal anti-nociceptive state intraoperatively, we will also examine whether there is any reduction in pain in PACU, using the numerical rating score and opioid requirements as the markers of this outcome. We will also record any requirement for naloxone reversal of opioid effect as a marker of excessive opioid administration.

##### Further clinical outcomes

Quality of recovery (day 1 and day 30) – QOR-15Modified Brice Interview (day 1 and day 30)Hospital length of stay and discharge destinationDays alive at home 30 days after surgerySerious adverse events (falls, unplanned high-dependency or intensive care unit admission, stroke or myocardial infarct, surgical site infection, hospital readmission and death) up to 12 monthsCognitive status at 12 months (telephone Montreal Cognitive Assessment (tMOCA))

The QOR-15 is a validated score reflecting overall quality of recovery from anaesthesia and surgery [22, 23]. The Modified Brice Interview [24, 25] is used to check for awareness with recall. Days alive at home (DAAH) has been chosen as a validated patient-centred outcome measure that is readily quantifiable and reflects duration of hospitalisation, discharge destination and mortality [26]. Serious adverse events will also be recorded, from patient report and note review out to 12 months postoperatively to look at longer-term recovery and later serious complications. We will also conduct a tMOCA at 12 months as a final cognitive evaluation [27].

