### Supplementary routine data collection

#### Baseline data

Use of hearing and visual aids will be recorded and these made available to the patient for the PACU assessments. We plan to collect standard demographic data including American Society of Anesthesiologists (ASA) score and planned surgery. Cognitive impairment is a known risk factor for the development of postoperative delirium [20] and will be used to stratify randomisation. The MOCA will be used to quantify cognitive status pre-operatively. In addition, some items from the 3D-CAM will be assessed at baseline to determine whether later errors in the 3D-CAM in PACU reflect a change from baseline performance. Pre-operative pain and anxiety will be recorded using the relevant questions from the QOR-15 questionnaire. The National Surgical Quality Improvement Programme (NSQIP) surgical risk calculator surgical complications risk [28] will also be calculated for each patient to potentially allow for risk adjustment in statistical analyses.

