### Statistical analysis and power calculations

We intend to recruit 600 participants. The 2 × 2 factorial design will result in 300 patients assigned to the maintenance phase intervention and 300 to the emergence phase intervention (see Fig. 1). This will ensure that the study will be well-powered for the primary EEG outcomes and sufficiently powered to detect moderate-large effects in the secondary clinical outcomes. Our primary analyses will be intention to treat; however, per-protocol analyses will also be reported. For the primary outcome for the maintenance phase *Alpha Max* intervention, alpha power in groups A and B (Fig. 1) pooled together will be compared to groups C and D. For the primary outcome for the emergence phase intervention, groups A and C (Fig. 1) will be compared to groups B and D pooled. The crude difference will be reported as the primary outcome; however, an adjusted estimate will also be provided for the emergence outcome. This will include an interaction term for the maintenance phase intervention, since one might reasonably expect alpha power in the emergence phase to correlate with alpha power in the maintenance phase.

EEG analysis will be performed using customised script in MATLAB. Our previous summary data suggest that a mean oscillatory alpha power of 4.75 dB with standard deviation of 2.1 dB might be expected in a general surgical population. Therefore, an estimated 230 patients are required to have 95% power to detect an increase in oscillatory alpha of at least 1 dB (equivalent to ~ 20% relative increase in alpha power in response to the fentanyl) in the intervention group compared with the control group (two-tailed alpha 0.05, beta 0.05); thus, with a planned total of 300 patients per group we are comfortably overpowered for this outcome.

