PACU delirium is our clinical outcome of primary interest, as a marker of neurocognitive recovery from anaesthesia. In our previous observational study, the incidence of CAM-ICU-diagnosed PACU delirium was 16% in those over 60 years and in a subsequent departmental audit, the incidence of PACU delirium diagnosed using the NuDESC tool was around 20% in those aged 65 years and over. Given that the study inclusion criteria requires > 2 h of anaesthesia, study participants will likely in general be having more extensive surgery and longer anaesthesia than those in the previous study and audit; therefore, we conservatively estimate a 20% incidence of PACU delirium in the control groups. From our observational work, the presence of EEG alpha has an odds ratio of approximately 0.5 for PACU delirium (unpublished data). Five hundred and thirty-two patients would be required to demonstrate a decrease in PACU delirium from 20 to 10% with 90% power (two-tailed alpha 0.05, beta 0.1, *χ*^2^ test). Thus, the study is powered to demonstrate strategies which have a large impact in preventing the development of delirium.

Almost certainly this study will also be sufficiently powered for minimum clinically important effects in some of the other secondary outcomes including delirium subcomponent features, days alive and out of hospital, and quality of recovery. We plan to recruit 600 patients to allow for loss to follow-up and a lower incidence of delirium than expected.

Continuous outcomes will be assessed using *t* tests and analysis of variance (ANOVA), ordinal with rank sum, and categorical outcomes will be assessed using the *χ*^2^ test, with significance set at *p* < 0.05. Non-linear mixed-effect modelling will be incorporated where appropriate to account for propensities such as: patient maximum alpha power, within-patient fentanyl and desflurane dose-response relationships and characteristics of the anaesthetic technique. Interactions between the two interventions are possible and will be examined. We also plan to carry out multivariate logistic regression to determine the major risk factors for the development of the features of PACU delirium, and receiver operator curve analysis to determine which elements of the early delirium screening tools are most closely associated with adverse clinical outcomes. *We anticipate performing further exploratory analyses in addition to those explicitly defined pre-operatively.*

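### The stated tests would compare 12-month tMOCA without using the pre-operative MOCA; the comparison is valid, but precision is lost that baseline adjustment would recover at no cost (minor)

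*Protocol article*

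**What the plan says.** **Outcome.** Under Further clinical outcomes, the article lists cognitive status at 12 months, measured with the telephone form of the MOCA: "We will also conduct a tMOCA at 12 months as a final cognitive evaluation". It gives no named test, cut-off or change score for it.

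**Baseline.** Under Baseline data: "The MOCA will be used to quantify cognitive status pre-operatively". Under Randomisation and blinding, assignment is "stratified by cognitive status (determined by pre-operative Montreal Cognitive Assessment (MOCA) score", so the score must be known before a patient is randomised. It also has a part in screening: under Ethical considerations, a very low score can contribute to exclusion.

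**Tests.** Under Statistical analysis and power calculations: "Continuous outcomes will be assessed using *t* tests and analysis of variance (ANOVA), ordinal with rank sum", with chi-square for categorical outcomes.

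**Adjustment.** Three statements bear on it, and none places baseline MOCA in the analysis of tMOCA:
- For the primary EEG comparisons: "The crude difference will be reported as the primary outcome; however, an adjusted estimate will also be provided for the emergence outcome". The adjustment named there is for the other intervention.
- The NSQIP surgical risk score is collected to "potentially allow for risk adjustment in statistical analyses". This is optional and concerns a different variable.
- "Non-linear mixed-effect modelling will be incorporated where appropriate to account for propensities such as: patient maximum alpha power", followed by dose-response relationships and anaesthetic technique.

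A multivariate logistic regression is also planned, but its subject is risk factors for features of PACU delirium.

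**The concern.** The trial measures the same construct before surgery and at 12 months, and treats the first measurement as prognostic enough to stratify on. Whichever class tMOCA falls into, the stated test leaves that measurement out. The part of the 12-month spread that only reflects where patients started then stays in the standard error.

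Stratifying without adjusting adds to the mismatch. Stratification makes the arms more alike in baseline cognition, but a two-sample test computes its standard error as if they had not been made alike. The test becomes somewhat conservative and gives up part of what the stratification was meant to gain.

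What is at stake is the width of the interval for the tMOCA difference and the chance of detecting a modest effect on longer-term cognition, which the secondary objectives name. The primary EEG outcomes and PACU delirium are not affected.

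**Working it through.** **The plan's own figures.** The article states no SD, effect, sample size or power for tMOCA, so there is no tMOCA figure to reproduce. Its two sample sizes do reproduce: 1 dB with SD 2.1 dB at 95% power gives 115 per arm, 230 in all; 20% v 10% at 90% power gives 266 per arm, 532 in all (pooled variance, no continuity correction). Nothing stated is wrong in that respect.

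**Inputs**
- From the article: 300 v 300 for each factor; two-sided 5% level.
- Assumed, because the article gives none: correlation r between baseline MOCA and 12-month tMOCA, 0.3 to 0.7; 12-month loss 20%, leaving n = 300 × 0.8 = 240 per arm; true difference d = 0.2 SD.

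**Formulae**, for a difference in means with tMOCA in SD units
- Variance after adjustment, relative to unadjusted: 1 − r².
- Power = Φ( d / √[(1 − r²) × 2/n] − 1.96 ).
- Difference detectable with 80% power = (1.96 + 0.84) × √[(1 − r²) × 2/n].

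**Unadjusted, n = 240.** √(2/240) = 0.0913. 0.2/0.0913 = 2.19. Power = Φ(2.19 − 1.96) = 59%. Detectable difference 0.256 SD.

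**Adjusted, n = 240**

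| r | Variance removed | Power for 0.2 SD | Detectable difference (SD) |
|---|---|---|---|
| 0.3 | 9% | 63% | 0.244 |
| 0.5 | 25% | 72% | 0.221 |
| 0.6 | 36% | 78% | 0.205 |
| 0.7 | 49% | 87% | 0.183 |

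**Sensitivity to the loss rate.** With no loss (n = 300), power goes from 69% unadjusted to 73% (r = 0.3) and 93% (r = 0.7). With 30% loss (n = 210), it goes from 54% to 58% and 82%. The gain depends mainly on r and little on the loss rate.

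**Effect of stratifying without adjusting.** This was simulated with 510 patients analysed (15% loss) and two MOCA strata cut at the 25th or 50th percentile; the cut is assumed, as the article gives none. The unadjusted t test had a type I error of about 2% to 4% in place of 5%, while ANCOVA held about 5%. The unadjusted test therefore errs on the safe side.

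**Loss related to baseline score.** This was simulated with 300 per arm and 20% loss overall, the lowest baseline quarter lost at 40% and the rest at 13%.
- Same pattern in both arms: the unadjusted difference is unbiased, with type I error about 5%.
- Pattern in one arm only: bias of 0.05 SD (r = 0.5) to 0.09 SD (r = 0.8), with type I error 9% to 16%. ANCOVA on baseline removes this when loss depends on the baseline score alone.

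The formulae apply to a comparison of means. If tMOCA were handled by rank sum or chi-square, baseline would be ignored just the same, but the size of the loss would differ.

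**The case against.** The strongest reply is that the article never names the test for tMOCA, that covariates for one of many secondary outcomes normally belong in the statistical analysis plan, and that nothing here forbids adjustment. Much of this stands. A reader might infer that the article commits to a t test on the raw telephone score. It does not: that is one reading of a general rule, and the ordinal or categorical rule might apply instead. But the article does not simply stay silent. It states a test for each outcome class, and all of them are unadjusted. Naming a better method in their place is a fair comment on what is written.

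A reader might also infer that loss of cognitively impaired patients will bias the result. The documents do not support that. No difference in loss between arms is documented, loss that is equal in both arms causes no bias in the simulation above, and missing-data methods may lie in the analysis plan. Adjustment would not resolve deaths before 12 months either.

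It is equally tempting to say that baseline explains most of the 12-month spread. The document gives no correlation, and even r = 0.7 explains only 49%.

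Finally, the gain is small if r is low: 59% to 63% at r = 0.3. The trial makes no power claim for tMOCA, and stratification already limits chance imbalance. These points bear on severity; they do not make the unadjusted test the better choice.

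**Conclusion.** The point holds as a matter of efficiency and is minor. Under the stated rules, 12-month tMOCA would be compared without the baseline MOCA that the stratification requires for every randomised patient. That comparison is valid, and if anything conservative after stratified randomisation, but less precise than the data allow. Under the assumed correlations of 0.3 to 0.7, adjustment removes 9% to 49% of the variance; with an assumed 20% loss and a 0.2 SD effect, power moves from 59% to between 63% and 87%. Correlation, loss and effect are all assumptions, since the article supplies none of them. Protection against baseline-related loss that differs by arm is a possible side benefit of adjusting, not a defect shown in the plan. No primary or main clinical conclusion depends on this outcome.

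**What to change.** State that tMOCA at 12 months will be analysed by ANCOVA with pre-operative MOCA as a continuous covariate, together with both allocations and the stratification factors, and that the adjusted difference will be reported with its confidence interval for each intervention. Enter MOCA as a covariate and do not analyse tMOCA minus MOCA: the two are different administrations, and a covariate needs no common scale. Report by arm how many patients died or were not reached by 12 months, so that readers can judge any difference in loss.

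The cost is one sentence and one model. The baseline data are already collected, and sample size and follow-up do not change. Fixing it before allocation is revealed to the analyst also rules out a later choice among crude, change-score and adjusted results.
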